## Abstract

**Background:**

According to the Global Diabetes Plan, a unified health system with preventive and educational strategies is essential to proper diabetes care and primary settings should be the main site of care. In Brazil, there is limited access to outpatient hospital diabetes services, while primary-care diabetes support is underutilized. Telemedicine can be a useful adjunct to support discharge of stable patients with type 2 diabetes to the primary care setting. In this paper, we present a randomized controlled trial (RCT) protocol designed to evaluate the effects of telehealth support for stable type 2 diabetes patients discharged from hospital outpatient diabetes clinics.

**Methods:**

We designed a RCT. Patients with stable type 2 diabetes (glycated hemoglobin < 8%) considered eligible for discharge from specialized to primary care will be included. Those with uncontrolled ischemic heart disease, severe neuropathy, and stage IV/V nephropathy will be excluded. Enrolled patients will be randomized into two groups: follow-up supported by periodic phone calls by a nurse (intervention group) plus primary care or routine primary care only (control group). The intervention group will receive regular telephone calls (every three months for one year) and will have a toll-free number to call in case of questions about disease management. The main outcome measure is a comparison of glycemic control between groups (assessed by glycated hemoglobin) at one-year follow-up.

**Discussion:**

We plan to evaluate the effectiveness of a telephone-based intervention on glycemic control in patients with type 2 diabetes followed by primary care teams. Telemedicine can be an important adjunct in type 2 diabetes management, improving patient education and knowledge about the disease. Furthermore, it can help the healthcare system by alleviating overload in specialized care settings and supporting the stewardship role of primary care.

**Trial registration:**

Clinical Trials, NCT02768480. Registered on 29 April 2016.

**Electronic supplementary material:**

The online version of this article (doi:10.1186/s13063-017-1954-z) contains supplementary material, which is available to authorized users.

## Background

According to the International Diabetes Federation (IDF), in 2015, the global prevalence of diabetes was 415 million adults. Over 14.3 million of these adults live in Brazil, making it the country with the fourth largest number of persons living with diabetes [1]. Due to this large population of patients, mostly affected by type 2 diabetes, no health system can be planned without coordinating between primary and specialized care. The Global Diabetes Plan suggests that diabetes management in primary care could be key to achieving glycemic control and preventing chronic complications [2].

Brazil has experienced major changes in how healthcare is provided in the last 20 years: a structured and coordinated health system was created and primary care was defined as the main setting of healthcare. Despite these changes, the population has limited access to primary care, which has little problem-solving capacity, and specialized clinics are overcrowded.

Since 2007, TelessaúdeRS – UFRGS, a multiple-intervention telemedicine project, has been supporting primary care providers to improve management of chronic diseases. Our experience shows that many unnecessary referrals can be avoided through teleconsultations and training of primary care teams [3, 4]. We plan to explore whether telehealth strategies can have similar positive effects on patients being discharged from specialized to primary care. For the present project, we specifically aim to assess the effects of a simple remote monitoring strategy for the transition of type 2 diabetes care from specialized to primary facilities. This report follows the guidelines provided in the SPIRIT Statement [5]. We presented a standardized checklist with recommended items of SPIRIT Statement (Additional file 1).

## Methods

### Study design and settings

This open-label randomized controlled trial will seek to evaluate the effects of patient-directed phone calls as a means of supporting the care of individuals discharged from an outpatient hospital-based tertiary care diabetes clinic to primary care. The study will be performed at an outpatient diabetes clinic at Hospital de Clinicas de Porto Alegre, an academic hospital in southern Brazil. This hospital is a TelessaúdeRS partner in offering support to primary care.

### Eligibility criteria

#### Inclusion criteria

Patients eligible for the trial must comply with all of the following criteria at randomization: established diagnosis of type 2 diabetes; and HbA1c level < 8% (HPLC method).

All patients that meet the inclusion criteria above are able to enter in the randomization, regardless of the treatment in use to manage diabetes (diet, oral antihyperglycemic medication, or insulin). The research team will identify patients meeting the inclusion criteria.

#### Exclusion criteria

Patients with the following criteria will not be included in the study: stage IV or V nephropathy; uncontrolled ischemic heart disease; or severe autonomous or peripheral neuropathy.

### Intervention

Study flowchart, procedures and evaluations are depicted in Figs. 1 and 2. All patients will receive an illustrated brochure with information about diabetes care and a standardized discharge document. The discharge note will be directed to the primary care team and will present the patient’s medical history, current type 2 diabetes care regimen, individualized glycemic target, and management plan. The TelessaúdeRS toll-free number will also be mentioned in the discharge note as a tool for helping primary care manage the patient.

Patients randomized to the intervention group will receive a toll-free number to call nurses who can review their treatment and address any questions about their diabetes care. In addition, they will receive quarterly calls from the nurse team to review topics on diabetes education and non-pharmacologic and pharmacologic treatment. In the phone calls, nurses will do educational interventions, reviewing therapy adherence, side effects, techniques of insulin application, diet adherence, foot care, frequency of physician visits, and will give advices about hypoglycemia. Due to national legal restrictions, no treatment adjustments will be performed; therefore, if medication adjustments are needed, patients will be oriented to consult with the primary care provider.

Patients randomized to the control group will be followed exclusively by the primary care team. These patients will also receive follow-up phone calls at the same times as the intervention group (at three, six, nine, and 12 months), but without any diabetes intervention. If necessary, in both groups, treatment adjustments will be performed by the primary care physician, regardless of telemedicine actions.

### Outcomes

One year after enrollment, both groups will undergo a standardized evaluation of current diabetes management, health services support, and treatment adherence. All participants will also undergo blood and urine collection for laboratory assessment.

The primary outcome will be glycemic control measured by HbA1c. The following outcomes will also be evaluated: blood pressure control evaluation (after 5 min of seated rest); lipid control; number of severe hypoglycemia episodes; antiplatelet and statin therapy; number of physician, nurse, and dietitian appointments; rate of referral to tertiary care; current satisfaction with diabetes management; emergency visits because of acute complications of diabetes; treatment adherence; new or worsening nephropathy and peripheral neuropathy; major cardiovascular events; and death.

**Fig. 1 Fig1:**
[figure not shown]
Study *flowchart*: describes randomization and follow-up of participants

**Fig. 2 Fig2:**
[figure not shown]
SPIRIT figure: Summarizes the allocation, interventions, and outcomes of the study

### Sample size

We calculated a sample of 63 participants in each treatment arm to identify a between-group difference of 1% in HbA1c after one year, considering a standard deviation of 2%, an alpha of 0.05, and a statistical power of 80%.

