### Randomization and participant allocation

The random number sequence will be generated online (via randomization.com), using a 1:1 ratio, with blocks of four and six patients. The researcher responsible for randomization will not be involved in patient recruitment or enrollment. No stratification method will be used. Patients will be allocated sequentially, using dark-brown sealed envelopes, which will be opened only after patients have provided consent and the first assessment has been performed.

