## Discussion

Diabetes mellitus is a chronic condition associated with high mortality, reduced quality of life, and increased health cost. In particular, patients living in developing countries experience additional problems, such as poor support and limited access to healthcare services [6]. In this context, an integrated, multidisciplinary health system focused on prevention and education strategies is the key to provide adequate care to diabetic patients. Such integrated systems should focus on providing highly effective primary care, which should be able to treat the majority of diabetic patients, and refer only those with severe complications and refractory disease. Furthermore, clinical support through telemedicine interventions could strengthen primary care and enhance its quality [7].

Brazil has an excessive number of referrals and large waiting lists for referral to specialized care, with waiting times of months to years. Moreover, specialized services are unable to meet the demand for care, which leads to overloading of endocrinology clinics with unnecessary visits.

Our study aims to explore if we can improve the performance of primary care by supporting patients in the transition from specialized to primary care through the use of telehealth services. We aim to include well-controlled patients (defined as HbA1c < 8%) who no longer benefit from specialized care to glycemic treatment adjustment. We expect to answer whether a periodic, systematic intervention focused on education and adherence can improve diabetes control and whether this strategy can support management, maintaining, or improving the treatment offered in primary care. We will explore an innovative strategy to optimize the transition of care, based on a tool that has proven benefit in diabetes management. As future perspectives, if this intervention shows benefits to diabetic patients being discharged from specialized care, an economic assessment is planned to evaluate the costs of the intervention and to discuss with stakeholders the widespread implementation.

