In one previous study of low-income urban adults, periodic phone calls had a superior effect on glycemic control compared to printed education material (control). After one year, a significant decrement in HbA1c was demonstrated in the intervention group (–0.23% ± 0.11% versus +0.13% ± 0.13%; *p* = 0.04), with a better effect in patients who received more calls [8]. Similar results were found in a larger sample with fewer phone calls [9]. As expected, patients with the worst baseline glycemic control had greater reductions in HbA1c.

On the other hand, a recent meta-analysis of five studies that compared phone-call intervention with usual care in patients with type 2 diabetes showed a non-significant decrement of HbA1c values in the intervention group (pooled mean difference, –0.38%; 95% confidence interval, –0.91 to 0.16) [10]. Thus, the role of periodic educational phone calls on glycemic control remains unclear, despite some evidence for improvement [11].

Despite such evidence of improved glycemic control, long-term studies are lacking. The current literature has no information about the effects of such interventions on chronic complications of diabetes, cardiovascular events, or mortality, and the majority of studies have employed follow-up periods between six months and one year. A future long-term evaluation of the aforementioned outcomes is important to analyze the effectiveness of this intervention and decide if it is indeed useful to improve primary care, considering the cost benefit.

In summary, we believe that telehealth can be a useful tool for diabetes management, facilitating patient self-management and the transition from specialized to primary care. The results of this study will help us define whether telephone nurse support should be made widely available as a tool to reduce overcrowding of specialized services.

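### The stated 80% power holds only for a 1-point HbA1c difference with SD 2, which is 2.6 to 2.8 times the effects the protocol itself cites

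*Protocol article*

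**What the plan says.** The Sample size section of the protocol article plans 63 patients per arm. The target is a gap of 1 HbA1c point between the arms at one year, and the remaining inputs are given as "considering a standard deviation of 2%, an alpha of 0.05, and a statistical power of 80"%. The section gives no source or reason for either the difference or the SD. Allocation is "using a 1:1 ratio, with blocks of four and six patients" (Randomization and participant allocation), and Statistical methods names Student's t-test for normal continuous variables.

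The population is restricted at entry. Inclusion criteria require an "HbA1c level < 8% (HPLC method"), and the Discussion says: "We aim to include well-controlled patients (defined as HbA1c < 8%) who no longer benefit from specialized care to glycemic treatment adjustment".

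The Discussion also reviews the evidence:
- A one-year telephone trial is reported with HbA1c changes of -0.23 and +0.13 points.
- A meta-analysis of five studies "showed a non-significant decrement of HbA1c values in the intervention group", with a pooled difference of -0.38 (95% CI -0.91 to 0.16).
- On who benefits most, it says that "patients with the worst baseline glycemic control had greater reductions in HbA1c".

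**The concern.** The planned difference is far larger than anything the article cites for this kind of intervention. The article's own remark on baseline control points to smaller reductions in the patients it enrols. The planned SD of 2 points is also hard to square with a group whose entry values are all below 8%.

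What is at stake is how a null result is read. The Discussion says the findings will help decide whether nurse telephone support is offered widely. A reader who sees 80% power and a non-significant result may conclude that the calls do not work, when the trial may have had little chance of detecting an effect of the size already reported.

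**Working it through.** **Inputs.** From Sample size: n = 63 per arm, difference 1, SD 2, alpha 0.05 (taken as two-sided), power 80%. From the Discussion: 0.23 + 0.13 = 0.36 for the single trial and 0.38 for the meta-analysis. SDs below 2.0 are assumptions, because the article gives no other SD. The ± values of the single trial behave as standard errors: 0.36 / sqrt(0.11² + 0.13²) = 2.11, p about 0.035 against the reported 0.04. They therefore supply no SD.

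**Step 1: reproduce the stated figure.** n per arm = 2 × (1.960 + 0.842)² × SD² / difference² = 2 × 7.85 × 4 / 1 = 62.8, rounded up to 63. Power at 63 is 80.1%. (The t-test version gives 64 per arm, and 79.5% at 63. A one-sided alpha of 0.05 gives 50 and does not reproduce the figure.) The calculation is correct for its inputs, which amount to a standardized difference of 0.5.

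**Step 2: compare the difference with the cited effects.** 1 / 0.38 = 2.6 and 1 / 0.36 = 2.8. The far end of the cited interval is 0.91, so 1 point lies outside it by 0.09.

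**Step 3: power at 63 per arm.** The standard error of the difference is SD × sqrt(2/63) = 0.178 × SD. Power = Φ(difference / (0.178 × SD) − 1.960). The difference detectable with 80% power is 2.80 × 0.178 × SD = 0.499 × SD.

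| SD | Power at 0.36 | Power at 0.38 | Power at 1 | Detectable difference |
|---|---|---|---|---|
| 2.0 (planned) | 17% | 19% | 80% | 1.00 |
| 1.5 | 27% | 30% | 96% | 0.75 |
| 1.2 | 39% | 43% | over 99% | 0.60 |
| 1.0 | 52% | 57% | over 99% | 0.50 |
| 0.8 | 71% | 76% | over 99% | 0.40 |

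At the far end of the cited interval (0.91) with SD 2.0, power is 72%.

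**Step 4: the SD that would restore 80%.** 0.36 / 0.499 = 0.72 and 0.38 / 0.499 = 0.76.

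**Step 5: is SD 2 plausible?** If entry values run from an assumed 5% up to 8%, the SD cannot exceed (8 − 5)/2 = 1.5. An even spread gives 3/sqrt(12) = 0.87. So SD 2 cannot hold at entry. To reach 2 at one year from a baseline SD of about 0.9, change during follow-up would need an SD of about sqrt(2² − 0.9²) = 1.8, if the two parts are independent. That is doubtful but possible.

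**The case against.** The strongest reply has four parts.

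*The target may be deliberate.* One point can be read as the difference worth detecting, not a forecast, and the rationale may sit in a fuller protocol. This stands as far as it goes, so the missing rationale is not itself the fault. It does not alter the power at the effects the article cites.

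*The cited effects are imperfect anchors.* They are not described as coming from patients leaving specialist care. Control patients may deteriorate after discharge to a system that the Background calls limited, and the remark on baseline control concerns reductions, not prevented worsening. A confidence interval for a pooled mean also does not bound the effect in a new setting. All of this stands. A reader might infer that 1 point requires one arm to move by a full point. It does not, since both arms can move, as in the cited trial. But the article does not say that it relies on control-arm deterioration.

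*The SD does not contradict the entry limit.* A reader might infer that it does. The limit caps HbA1c at randomization, while the calculation concerns one year later. An SD that is too large is also conservative at the 1-point target. This stands: the two doubtful inputs push power in opposite directions.

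*A non-significant result is not shown to be the likely one.* A reader might infer that it is. At 0.38 this requires an SD above about 0.38 / (1.96 × 0.178) = 1.1, and at SD 1.0 the power is 57%. The document does not settle which side of 1.1 the one-year SD falls on.

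**Conclusion.** The sample size arithmetic is sound. What does not hold is the 80% as a general description of the trial, because it belongs to a 1-point difference with SD 2 only. For the 0.36 to 0.38 points that the article cites, power is 17-19% at the article's own SD and between 27% and 76% over assumed SDs of 1.5 to 0.8. It stays under 80% for any SD above about 0.76. The true power cannot be fixed from the document, because neither the one-year SD nor the course of the control arm is known.

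The comparison of the planned difference with the cited effects rests directly on the text. The doubt about SD 2 is an inference that uses an assumed lower limit of 5%. The figures assume a two-sided 5% test, equal SDs in the arms and 63 analysed patients per arm.

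**What to change.** Keep the sample size. At the planned SD, 80% power for the cited effects would take 435 to 485 per arm, and at SD 0.8 it would take 70 to 78, so the SD needs to be known before the number is judged.

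1. In Sample size, state that the 80% applies to a 1-point difference with SD 2 only, and give the reason for that target, including any reliance on deterioration in the control arm.
2. Add the detectable difference and the power at 0.36 to 0.38 points, either over a range of SDs or at the pooled SD of 12-month HbA1c, computed without arm labels from patients who have completed follow-up.
3. Analyse 12-month HbA1c adjusted for baseline HbA1c, which Data collection methods already records. The SDs in the table are then read as residual SDs.
4. Pre-specify, here or in the analysis plan, how a null result is read. For example: if the 95% CI for intervention minus control includes zero and any value from -0.36 to -0.38, the result is reported as inconclusive and not as no effect. The rule can discriminate: around an estimate of zero the interval would be ±1.96 × 0.356 = ±0.70 at SD 2.0, but ±1.96 × 0.178 = ±0.35 at SD 1.0, which just excludes the cited effects.

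The cost is a text change and one blinded calculation, with no extra patients. The downside is a less favourable stated power.

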### Recruitment

Study monitors will be responsible for identifying eligible patients at the time of discharge. After discharge, the research team will explain the study procedures and will invite eligible patients to join the study. After providing written informed consent, the patients will be randomized to the intervention (primary care with nurse-led telephone support) or control (primary care alone) groups. Patients will complete a standardized questionnaire and undergo clinical and laboratory assessment.

### Randomization and participant allocation

The random number sequence will be generated online (via randomization.com), using a 1:1 ratio, with blocks of four and six patients. The researcher responsible for randomization will not be involved in patient recruitment or enrollment. No stratification method will be used. Patients will be allocated sequentially, using dark-brown sealed envelopes, which will be opened only after patients have provided consent and the first assessment has been performed.

### Blinding

The study is not blinded for trial participants, care providers, or outcome assessors. Statistical analysis will be performed in blind fashion.

### Data collection methods

Study personnel will collect baseline data with a standardized questionnaire. Blood pressure will be measured after a 5-min rest. Information about foot sensitivity, ophthalmologic evaluation, glycemic control (HbA1c, fasting glucose), renal function (creatinine, glomerular filtration rate [GFR], and albuminuria), and lipid profile will be obtained from medical records. Follow-up information will be collected with a standardized questionnaire by telephone quarterly to assess patient’s participation and minimize follow-up dropouts. After the completion of the study, the final assessment will be performed with a standardized questionnaire. The questionnaires will evaluate the following: demographic, ethnical, and education level data; drug or alcohol use; treatment of diabetes; cardiovascular history; associated co-morbidities; hospital admissions; and smoking status. Furthermore, the final questionnaire will evaluate the treatment satisfaction, emergency visits for a diabetes reason, rate of hypoglycemia, number of primary care visits to review diabetes, and rate of referrals to tertiary care. The Brief Medication Questionnaire will be used to assess adherence and comprehension of therapy on baseline and follow-up. Blood pressure, body weight, and height and foot exam will be performed and blood and urinary samples will be collected.

### Statistical methods

Variables with normal distribution will be presented as means ± standard deviation; asymmetric variables will be presented as median and interquartile range. Categorical variables will be presented as total counts and percentages. Normal continuous variables will be compared with Student’s t-test and categorical variables will be compared with the chi-square test. No interim analysis is planned. Main outcomes will be presented both with intention-to-treat (all randomized patients) and per-protocol (patients who received at least one telephone contact) analyses. We will use Cox regression for outcome analysis.

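### No model is assigned to one-year HbA1c, and the only stated method that fits it, an unadjusted t-test, leaves the collected baseline HbA1c unused

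*Protocol article*

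**What the plan says.** All references are to the protocol article.

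- **Outcomes:** "The primary outcome will be glycemic control measured by HbA1c". The Abstract places the comparison at one year, so the outcome is one continuous value per patient.
- **Statistical methods:** "Normal continuous variables will be compared with Student’s t-test". Categorical variables get a chi-square test. Asymmetric variables are to be summarised by median and interquartile range, but no comparison is named for them. A closing sentence gives Cox regression as the method for outcome analysis, without saying for which outcomes. No covariate is mentioned.
- **Sample size:** 63 per arm to "identify a between-group difference of 1% in HbA1c after one year", "considering a standard deviation of 2" per cent, with "an alpha of 0.05, and a statistical power of 80" per cent.
- **Inclusion criteria:** HbA1c below 8% must be met at randomisation. Patients enter "regardless of the treatment in use to manage diabetes (diet, oral antihyperglycemic medication, or insulin").
- **Data collection methods:** the baseline items taken from medical records include "glycemic control (HbA1c, fasting glucose), renal function" and lipids.
- **Randomization and participant allocation:** 1:1 in blocks of four and six. "No stratification method will be used".

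**The concern.** A reader of the Statistical methods section cannot tell which analysis decides the trial. The t-test line is general and conditional on normality. The Cox sentence is the only one directed at outcomes, yet it describes a time-to-event model. By elimination, one-year HbA1c falls to an unadjusted t-test, which is also the comparison on which the sample size rests.

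That choice ignores a covariate the trial already has. A baseline HbA1c should exist for every patient, because eligibility depends on it. The arms are not balanced on it by design either, since there is no stratification. Two things are given up: a smaller standard error, and correction of the estimate when the arms happen to start at different HbA1c levels. Tying the test to a normality judgement also lets the data choose the primary method.

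**Working it through.** **Inputs.** From Sample size: difference 1%, SD 2%, alpha 0.05, power 80%, 63 per arm. From the Discussion: pooled effect 0.38% in the cited meta-analysis. Not in the document, so assumed: baseline SD of HbA1c 0.5 to 1.0%, and the baseline to 12-month correlation ρ.

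**1. The plan's own figure.** n per arm = 2 × SD² × (1.96 + 0.842)² / difference² = 2 × 4 × 7.85 / 1 = 62.8, so 63. This reproduces the stated number with a two-sided test (a one-sided test would need 50). Power at 63 per arm is 80.1% by the normal approximation and 79.5% by the exact t calculation. The trial is therefore sized for an unadjusted comparison of two means, and that comparison gives about the planned power.

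**2. A plausible ρ.** With a regression slope of 1 and a follow-up SD of 2%, ρ = baseline SD / 2. A baseline SD of 0.5% gives 0.25 and one of 1.0% gives 0.50. A ρ of 0.6 would need a baseline SD of 1.2% among patients who all start below 8%, which is unlikely.

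**3. Effect of baseline adjustment.** The residual SD becomes 2 × √(1 − ρ²). Power at 63 per arm for a 1% difference:

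| ρ (assumed) | Residual SD | Power, normal approx. | Power, t-based | n per arm for 80% (normal approx.) |
|---|---|---|---|---|
| 0 (unadjusted) | 2.000 | 80.1% | 79.5% | 63 |
| 0.25 | 1.936 | 82.6% | 82.0% | 59 |
| 0.3 | 1.908 | 83.7% | 83.1% | 58 |
| 0.4 | 1.833 | 86.5% | 86.0% | 53 |
| 0.5 | 1.732 | 90.0% | 89.5% | 48 |

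**4. Chance imbalance.** The SE of the difference in baseline means is baseline SD × √(2/63) = baseline SD × 0.178, that is 0.09 to 0.18% HbA1c for a baseline SD of 0.5 to 1.0%. An imbalance of 1.96 SE moves the unadjusted estimate by ρ × 2 × 1.96 × 0.178 = ρ × 0.70. This is 0.17% at ρ = 0.25, 0.21% at 0.3 and 0.35% at 0.5, against a target of 1%.

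**5. At the effect cited in the Discussion.** For a difference of 0.38%, power (normal approximation) is 18.6% unadjusted, 20.0% at ρ = 0.3 and 23.3% at ρ = 0.5.

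**The case against.** The strongest case on the other side is that nothing stated is wrong. Under 1:1 randomisation the t-test is unbiased and keeps its alpha, and its standard error already allows for chance imbalance. Unstratified blocked allocation is a legitimate design. Covariates are often left to an analysis plan, which may exist but is not shown. The gain rests on a correlation the document does not give. The entry cap at 8% narrows the baseline range, and a baseline value from records with no stated timing could lower the correlation further. At ρ of 0.25 to 0.3 the gain is only about 2 to 4 points.

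Most of this stands and sets the size of the point. It does not remove it. The section lists its methods, only one of them fits the primary outcome, and the sample size uses the same unadjusted comparison, so this is more than silence left to a later document.

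Several stronger readings are tempting but unsupported:

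- **That the plan fixes the t-test as the primary analysis.** It assigns no test to HbA1c by name, and the Cox sentence sits beside it.
- **That planned power is lost.** The 80% is delivered; what is forgone is extra efficiency.
- **That 12-month HbA1c will be skewed enough to matter.** The document gives no distribution, and a comparison of means with 63 per arm generally tolerates moderate skew.
- **That imbalance in insulin use threatens the result.** If half the patients use insulin (assumption), a gap of 10 points or more between arms has about a 26% chance. If insulin users differed by as much as 1% HbA1c (assumption), a 10-point gap would shift the estimate by only 0.10 × 1% = 0.1%. The document does not say how strongly insulin use predicts the outcome.

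**Conclusion.** The point holds as a recommendation on efficiency and clarity, not as an error that invalidates the trial. The text leaves the primary outcome without a named model, and the one usable method it lists is valid but does not use baseline HbA1c.

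For ρ between 0.25 and 0.5, which assumes a baseline SD of 0.5 to 1.0%, a slope of 1 and the planned follow-up SD of 2%, adjustment raises power from about 80% to about 82 to 90% at a 1% difference. It also removes an error of roughly 0.2 to 0.35% in the estimate when the baseline imbalance reaches 1.96 SE. Adjustment is not a remedy if the true effect is near 0.38%: power there is about 19% without it and at most about 23% with it.

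**What to change.** State in Statistical methods, or in the analysis plan before the blinded analysis is opened, that the primary analysis of one-year HbA1c is a linear model (ANCOVA) with arm and baseline HbA1c as terms, used regardless of any normality check. Keep the unadjusted t-test as a sensitivity analysis. Limit Cox regression to time-to-event outcomes, and say which these are.

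Adding baseline insulin use as a covariate, and baseline-adjusting blood pressure and lipids in the same way, is optional.

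The cost is a sentence or two, with no new patients or data. The one weakness is reliance on a baseline HbA1c from medical records whose timing is not stated. An older value would reduce the gain but would not bias the comparison, provided it was measured before randomisation.
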